## 3. Results

The NET-PD project was funded in March 2022; data collection began in July 2022 and is currently in the recruitment phase, with two PD patients already enrolled. Data collection is expected to be completed in June 2024, and data analysis in October 2024.The results are expected for publication in December 2024.

## 4. Discussion

The cumulative frustration of TEMPO [23] and ADAGIO [41] investigations exemplifies the rough way to assess and postpone PD progression in clinical drug trials. Another challenge in developing clinical trials for neuroprotection is that in vivo brain neuronal counts are not available; therefore, no methods exist to monitor neuroprotection in the clinic. A TMS intervention and a delayed-start design may be able to address some of these problems. Several clinical trials have demonstrated the therapeutic benefits of TMS and TBS.As a novel form of excitatory TMS protocol, iTBS is less time-consuming and more effective than standard rTMS [42]. Another advantage is that TMS can be paired with EEG and EMG at the same time to monitor neuronal excitability as well as cortical function for PD patients. As well as better interpreting disease-modifying effects, delayed-start designs are reliable experimental designs for assessing neuroprotection. Once a month, the investigators, PD experts, and ethics committee will meet in person or online to discuss the trial’s progress and patient’s safety. The NET-PD trial is led by the Department of Neurology, Ruijin Hospital (PI: [name]), and is under the supervision of the Clinical Research Center, Shanghai Jiao Tong University School of Medicine.

Through this delayed-start, randomized, double-blind, sham-controlled trial, we hope to quantify the neuroprotective effect of iTBS in PD patients.

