### 2.2. Study Design

NET-PD is a 2-year prospective single-center, double-blind, multi-arm, delayed-start, sham-controlled trial. The study is conducted in two stages—the pseudo-controlled and active-treatment stage—with each stage consisting of a 2-week intensive phase and a 12-week maintenance phase, for a total of 14 weeks. The intensive period involves daily or twice-daily iTBS (or pseudo-stimuli) per week, for a total of 10 or 20 sessions, and the maintenance period consists of 12 weeks of iTBS (or pseudo-stimuli) once or twice a day, 2 days a week, for a total of 24 sessions in the single-stimulation group or 48 in the double group. In stage 1 (pseudo-controlled stage), patients are randomly assigned to one of four intervention groups in a 1:1:1:1 ratio: early-start single iTBS group (A1), early-start double iTBS group (A2), delayed-start single iTBS group (S1), and delayed-start double iTBS group (S2). The early-start groups conduct active iTBS throughout, whereas the delayed-start groups use pseudo-stimuli in the first stage and start using iTBS in the second stage. The only difference between the single- and double-stimulation group is the number of sessions per day: once daily for the single group and twice daily for the double group. In stage 2 (active treatment stage), participants in A1 and A2 continue to receive the same iTBS protocol as the first stage, while those in S1 and S2 start to receive active iTBS. All patients are required to have a detailed follow-up clinical assessment and electrophysiology record at baseline, 2 weeks, 14 weeks, 16 weeks, and 28 weeks. MRI and peripheral blood are collected at baseline, 14 weeks, and 28 weeks (Figure 1, Table 1). Each patient will spend 7 months in this study and the total duration of the research will be approximately 2 years, from July 2022 (first in) to December 2024 (last out) (Figure 2).

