### 2.5. Withdrawal Criteria

Subjects may withdraw at any time if anything occurs that may jeopardize their interests. Subjects who discontinue the study will no longer be covered by continued data collection. The reason for termination or withdrawal should be documented in the case report form. Patients should withdraw from the trial immediately if they meet the following criteria:Poor compliance to the protocol;Occurrence of an intolerable adverse event;Patients decline further treatment or follow-up;Loss of visits due to unavoidable situations, such as death;The investigators terminate the subject’s continued participation after review.

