### 2.14. Baseline Assessments and Follow-Up Evaluations

After screening, all the eligible patients will undergo a comprehensive detailed assessment, including basic demographic, motor and non-motor symptoms, α-syn in the peripheral blood, and resting functional MRI, EEG, and EMG. All the physicians involved in assessment receive consistency training prior to the start of the trial to ensure the uniformity of the standard. Basic demographic information including gender, age, education, concomitant diseases, family history, medication usage, etc. is taken. All motor symptom assessments will be video-numbered and scored by two independent physicians. Various aspects of the patients’ clinical symptoms are measured using Unified Parkinson Disease Rating Scale (UPDRS), Berg Balance Scale (BBS), Hamilton Depression Scale (HAMD), Hamilton Anxiety Scale (HAMA), MMSE, Montreal Cognitive Assessment (MoCA), Pittsburgh sleep quality index (PSQI), 39-item PD Questionnaire (PDQ-39), 16-item odor identification test from Sniffin’ Sticks (SS-16), Scale for Outcomes in Parkinson’s disease for Autonomic Symptoms (SCOPA-AUT), and Wexner constipation scale. At the same time, we draw the patient’s peripheral blood for cytology, biochemistry, and coagulation tests and to detect α-syn in exosomes. After two intensive phases (week 2 and week 16), patients will receive a brief follow-up evaluation including the UPDRS, EMG acquisition and side effects. At midterm (week 14) and the endpoint of the experiment (week 28), the patients must complete the same detailed set of evaluations as the baseline.

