### 2.15. Outcome Measures

According to the results of previous large delayed-start design disease-modifying drug studies, the neuroprotective effect can be commonly reflected by the difference in the changes in the UPDRS score before and after treatment between groups [22,39]. In an NET-PD study, the primary outcome is the differences in changes in UPDRS scores in the four groups before and after the iTBS intervention. As a secondary outcome, we will evaluate the effects of iTBS treatment on clinical symptoms, motor symptoms such as gaiting and postural balance, and non-motor symptoms such as mood, cognition, olfaction, and sleeping condition in PD patients. As a neuro-modulation intervention study, EEG, EMG and MRI images can also be visualized to indicate the functional activity status of the brain. The safety of the treatment will be assessed using a self-administered side effect scale. Additionally, self-administered side effects scales will be used to assess iTBS safety.

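### Each 12-week maintenance phase, with 71% of a stage's sessions, gets one scheduled side-effect reading per patient, taken when the phase ends

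*Protocol article*

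**What the plan says.** Section 2.15 names the safety instrument: "The safety of the treatment will be assessed using a self-administered side effect scale". Table 1 marks side effects at Visits 1 to 4, that is, weeks 2, 14, 16 and 28. Section 2.14 confirms the two earlier readings in each stage: "After two intensive phases (week 2 and week 16), patients will receive a brief follow-up evaluation including the UPDRS, EMG acquisition and side effects". The readings at weeks 14 and 28 rest on Table 1.

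Section 2.2 gives each stage a 2-week intensive phase of 10 or 20 sessions. A 12-week maintenance phase follows, with stimulation "once or twice a day, 2 days a week, for a total of 24 sessions in the single-stimulation group or 48 in the double group".

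Section 2.5 ends data collection for anyone who discontinues and asks for the reason in the case report form. Its grounds for immediate withdrawal include "Occurrence of an intolerable adverse event" and "The investigators terminate the subject’s continued participation after review".

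Section 4 describes the oversight: "Once a month, the investigators, PD experts, and ethics committee will meet in person or online to discuss the trial’s progress and patient’s safety".

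**The concern.** The scale is dense where treatment is short and sparse where treatment is long. It is read straight after each 2-week intensive phase, then not again until 12 further weeks of stimulation are over. Two things follow for the safety data.

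- Section 2.9 names discomfort or pain as the complaints reported in earlier work. These tend to be brief and tied to a session. One reading at the end of 24 or 48 sessions is a weak way to count them or to place them in time.
- A patient who leaves during maintenance leaves before the reading for that phase. Under Section 2.5 nothing more is collected, so the case report form holds a reason for leaving but the scale may hold nothing. If some of these patients leave because of side effects, the scale data will lean towards those who tolerated treatment.

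The single and double groups differ only in sessions per day, so any description of tolerability by group would rest on these few readings.

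**Working it through.** **Inputs.** Scale readings at weeks 2, 14, 16 and 28 (Table 1). Sessions per stage: 10 or 20 intensive, and 24 or 48 maintenance on 2 days a week for 12 weeks (Section 2.2). Sample of 60 and dropout of about 10% (Section 2.17). Data collection from July 2022 to June 2024 (Section 3); last patient out in December 2024 (Section 2.2).

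**Intervals for one patient.** From week 2 to 14 is 12 weeks, from 14 to 16 is 2 weeks, and from 16 to 28 is 12 weeks.

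**Share of treatment covered by one end-of-phase reading.**
- Single groups: 24 / (10 + 24) = 24/34 = 0.706.
- Double groups: 48 / (20 + 48) = 48/68 = 0.706.
- In time: 12/14 = 0.857 of the weeks in a stage.

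**A patient who stops mid-phase (illustration).** Suppose the patient stops at week 8. The last reading was at week 2. Since then there have been 6 weeks × 2 days = 12 sessions (single) or 24 (double) with no scale reading, and none follows. At the assumed dropout, 0.10 × 60 = 6 patients would leave at some point. How many would leave in maintenance, or because of side effects, is not given.

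**Does the monthly meeting lack data?** The trial schedules 60 × 4 = 240 readings. Over 24 months that is 240/24 = 10 a month; over 30 months it is 240/30 = 8 a month. A simulation assumed entry spread evenly and no dropout. It gave about 13 to 14 readings a month in mid-trial over 24 months, and about 10 over 30 months. The expected number of months with no reading was about 0.3 of 24 or 0.6 of 30, nearly all in the first or last three months. The 12-week gap therefore exists for each patient but not for the trial as a whole.

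**Effect of readings every 4 weeks in maintenance.** Adding weeks 6 and 10, and 20 and 24, cuts the longest interval from 12 weeks to 4. Each reading then covers 4 × 2 = 8 sessions (single) or 16 (double), instead of 24 or 48.

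**The case against.** A reader might infer three stronger points. The document supports none of them.

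- **The monthly reviewers have nothing new to look at.** This mistakes a gap in one patient's record for a gap in the trial's. Entry is rolling, and the counts above show new readings at almost every meeting.
- **The two schedules contradict each other.** Section 4 says that the meeting discusses progress and safety. It does not promise a monthly reading from each patient. A review held more often than a patient's visits is not an inconsistency.
- **Nobody has a trigger to act on.** Section 2.5 gives grounds for withdrawal that apply at any time and are not tied to a visit. A trial-level rule, and the reporting of events between visits, are matters that an article commonly leaves to the full protocol. Their absence here is no finding.

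The other side also has fair points against the narrower concern. Patients attend on 2 days a week, so events may be noticed and reported outside the scale. The recall period of the scale is not stated, and no formal comparison of safety between single and double groups is announced. Section 2.9 reports good tolerance in earlier studies. The 71% counts sessions, not missed events. All of this stands, and it makes the point modest. It does not remove it: the article fixes both the instrument and its four dates, and that schedule gives one structured reading for most of the treatment.

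**Conclusion.** The point holds as a modest improvement to safety data collection, not as an error or contradiction in the plan. The scheduled scale gives one reading per patient, at the end, for a 12-week phase containing 71% of a stage's sessions. Brief effects may be poorly captured, and patients who discontinue mid-phase may have no reading for that phase.

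This rests on Table 1 being the complete schedule for the scale. If the full protocol already has the scale completed at stimulation attendances or at discontinuation, the point is met. The size of any under-reporting cannot be computed from the document, since it gives neither the recall period nor an expected rate of side effects. The finding on the monthly meeting assumes roughly even accrual; clustered entry would leave more months without a reading.

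**What to change.** In Table 1 and Section 2.14, add completions of the existing self-administered scale within each maintenance phase, for example about every 4 weeks, at attendances patients already make for stimulation. Add one completion at discontinuation, and let Section 2.5 allow for it. State that the readings go to the existing monthly meeting in coded or pooled form, so that blinding is kept. The 4-week spacing is only an example; the trial team may choose another that shortens the 12-week interval.

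The cost is two or three short completions per patient per phase. For 60 patients and two phases that is 60 × 2 × 2 = 240 to 60 × 2 × 3 = 360 extra forms, plus one for each patient who discontinues. No new visit, staff or committee is needed, and the downside is a little patient time.

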## Figures and Tables

**Figure 1 jcm-11-04972-f001:**
[figure not shown]
Schematic representation of study outline and visits. Stage 1 = pseudo-controlled stage, Stage 2 = active treatment stage; Phase 1 = intensive phase, Phase 2 = maintenance phase; A1 = early-start single iTBS group, A2 = early-start double iTBS group, S1 = delayed-start single iTBS group, S2 = delayed-start double iTBS group.

**Figure 2 jcm-11-04972-f002:**
[figure not shown]
The NET-PD study flowchart.

**Table 1 jcm-11-04972-t001:** Outline and timelines of the trial.

	Screening	Baseline	Visit 1	Visit 2	Visit 3	Visit 4
	−2 Weeks	0	2 Weeks	14 Weeks	16 Weeks	28 Weeks
Written informed consent	×					
Inclusion/exclusion criteria	×					
Randomization		×				
Basic demographic		×				
Hoehn–Yahr stage		×	×	×	×	×
UPDRS		×	×	×	×	×
BBS		×		×		×
HAMD		×		×		×
HAMA		×		×		×
MMSE	×			×		×
MoCA		×		×		×
PDQ-39		×		×		×
PSQI		×		×		×
SS-16		×		×		×
SCOPA-AUT		×		×		×
Wexner		×		×		×
MRI	×	×		×		×
EEG		×		×		×
EMG		×	×	×	×	×
Blood test	×	×		×		×
Compliancy		×		×		×
Medication usage	×	×	×	×	×	×
Side effects			×	×	×	×

×, conducting evaluations.
